#### Spatial span

The Spatial Span test assesses a participant’s working memory in two phases, a practice phase and a test phase. It is based upon the Corsi Block-Tapping Task, in which a participant would mimic the order a researcher taps on a series of wooden blocks [40]. In this test, participants are asked to register a sequential series of coloured circles, that fill in outlines of circle shapes on the screen, and then immediately recall this sequence in the correct order.

The participant will be shown the correct sequence first, then asked to repeat the sequence, by clicking on the individual circles; see Fig. 3. In both modes (practice and real), the number of circles in the sequence is increased from a level of 2 at the start of the test to a final level of 9. In the bottom right-hand corner of the screen there is a notification of how many circles will be coloured in the task, for example “2 CIRCLES”. Circles are only coloured yellow for 500 ms, with a gap of 750 ms between the previous coloured circle going blank and the next circle becoming coloured. There are three possible sequences at each level, but as soon as the participant passes a sequence at each level (e.g. the 3-circle sequence) they will immediately progress to the next level (e.g. 4-circle sequence), not necessarily performing all three sequences at each level. As soon as the participant clicks an incorrect circle, they are informed of their error and given a second (and third if necessary) opportunity to attempt the test again with the same number of circles but a different sequence. If all three sequences at any level are completed unsuccessfully, the test will terminate.

**Fig. 3 Fig3:**
[figure not shown]
Spatial Span test; the participant is shown a sequence of yellow circles and then asked to repeat the sequence by clicking on the circles. The length of sequence increases each time a sequence is correctly recalled, up to a maximum of 9 circles

The parameters calculated include: spatial span length score, which is the longest sequence correctly recalled by the participant; total miss errors, which is the total number of times the participant missed selecting the correct circle in the test phase; total usage errors which is the total number of times the participant selected an incorrect circle in the test phase; reaction time, which is the time between the last circle of the sequence being presented and the first circle of the recalled sequence being selected; inter-circle movement time; which is the time taken to move from one circle to the next in recalling the sequence and total sequence movement time, which is the time taken to complete recalling each sequence.

### Oro-motor and language abilities

It is well recognised that language impairment is an early feature of AD – with deterioration in particular in naming and verbal fluency. Lesser known, are potential correlations between the motor aspects of speech production and voicing and how these may relate to the preclinical phase of AD [41–44]. To capture a broad range of speech and voice in a short period of time, we have included a standard picture describing task. Participants are shown the ‘Cookie Theft’ picture from the Boston Diagnostic Aphasia Examination [41] and asked to verbally describe it. This black and white line-drawn image conveys a complex scene of a woman and two children in a kitchen with interacting objects in which various activities are occurring. Participants are shown the following instructions: *“Below you see a picture of a scene. Please press the “Start recording“ button (below the image) and, in your own words, describe what you see in the most detail you can. Try to talk for at least a minute. When done, press “Stop recording“, and then “Submit””.* There is no time constraint on this task, although participants are encouraged to speak for at least 1 min. Participants' responses will be audio-recorded by the computer microphone for post-hoc analyses of their lexical, pragmatic, semantic and syntactic verbal proficiency using custom-written software programs. Deep learning approaches will be used to automate this process and to learn associated features.

### Further data collected

Data will also be collected on age, sex, years of education, English as first language, dominant hand, motor and cognitive symptoms, levels of pain and anxiety, and neurological diagnoses (Supplementary file 1). The following passive data will be collected without user input: log in time, log out time, user’s real-time mouse track, click actions on website internet browser (Chrome/Firefox/Safari etc). By collecting times of start/stop button clicking, we can understand how participants behave when they are using the application. For example, if a participant clicks start and stop several times, this means that the recording process may be difficult for participants to use. Time of day may influence performance. The following system-related data will be collected: Internet Protocol Version 4 (IPV4) address, browser information (name, version, product, manufacturer, layout), operating system, computer screen resolution, webcam information (resolution and frame rate). By collecting system information, such as browser information (version, product, manufacturer, layout), operating system (version, platform), camera resolution, video upload time, we can evaluate how different system environments may affect application administration.

### Aim 2

To validate TAS Test to prospectively estimate 5-year risks of cognitive decline and AD.

#### Design

We will undertake a prospective 5-year cohort study. We will invite 10,000 adults from a long-term cohort to complete online tests at home: (i) TAS Test every 12 months, and (ii) Cambridge Neuropsychological Test Automated Battery (CANTAB) [42] cognitive tests every 24 months. The prospective ‘high risk’ predictions of TAS Test will be validated against CANTAB, and clinically via in-person testing in a subsample of 300.

#### Participants

All eligible participants in The Island Study Linking Ageing and Neurodegenerative Disease (ISLAND) will be invited to take part in the TAS Test project. ISLAND is a 10-year public health initiative that launched in 2019 at the University of Tasmania (ethics reference H0018264). The project aims to recruit 20,000 people over 50 years of age who live in Tasmania, Australia by the end of 2022 and decrease their dementia risk; the detailed protocol is described in Bartlett et al. [43]. Nearly all assessments for the ISLAND project (except blood-based biomarkers that are collected in the research centre) are administered via an online portal where participants use a password to log in to their profile and complete a variety of assessments that are launched by the research team every few months. ISLAND participants complete extensive health questionnaires at baseline and will also be invited to complete TAS Test annually and CANTAB biennially, all online.

To date, over 13,500 participants have been recruited. CANTAB tests of cognitive function have been collected from approximately 3500 participants, TAS Test assessments from approximately 2200, and blood samples for the ApoE4 gene and blood biomarkers have been collected from approximately 2000. We can thus track cognition over time and identify people with scores indicative of cognitive decline as the sensitivity/specificity of CANTAB for classifying MCI and early dementia are 97/81% and 82/97% respectively [33].

The inclusion criteria for the TAS Test Aim 2 study are: ISLAND participants who have completed ≥2 TAS Test and ≥ 2 CANTAB tests. Exclusion criteria are: probable, or known, diagnosis of dementia or neurological disorders that impair hand function, speech or language function (e.g. stroke, Parkinson’s disease, collected through the baseline and interval ISLAND online health questionnaires). Participants will be classified as having ‘stable’ or ‘declining’ cognitive trajectories depending on PAL total errors at baseline (30 or more) and an increase of more than 10 total errors at follow-up assessments, as defined by Fowler et al. [44].

A sub-sample of 300 people will be selected from the main ‘TAS Test Aim 2’ cohort to attend the linked ISLAND Cognitive Clinic; this clinic provides facilities and expertise for gold standard clinical consensus diagnosis in a ‘one-stop’ interdisciplinary clinic where participants will have neuropsychological, and geriatrician or neurologist assessments, MRI brain scans, and ApoE4 tests. To select this cohort of 300 people for further face-to-face assessments from the larger cohort of up to 10,000 participants, we will invite 200 ISLAND participants (randomly selected) from those who have CANTAB scores (at the 48 month test point) indicative of MCI or AD – ie those with learning/working memory or attention cognitive deficits. A further 100 will be selected as age- and sex-matched controls from the Aim 2 participant cohort (using stratified random sampling) that comprises people with CANTAB scores indicative of unimpaired cognition.

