#### Measurements

We will extract baseline demographics and health survey data, 12-monthly TAS Test data, and CANTAB tests at baseline, + 24, and + 48 months.

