To validate prospectively against cognitive decline, we will assess the sensitivity and specificity of TAS Test to predict cognitive trajectories (“stable” and “declining”) using ROC curve analysis. We will estimate 5-year cognitive decline/MCI/AD risk using baseline TAS Test data in a sub-sample of 300 people. Clinical diagnostic categories are: cognitively unimpaired, MCI, and AD. Covariates considered in the model will include age, sex, ApoE4, years of education, and handedness. We will use Bayesian multinomial logistic regression with regularizing priors to estimate the covariate adjusted log-odds of being in each diagnostic category at 5 years as predicted by baseline TAS Test results. The resulting prediction model will estimate posterior highest density intervals for 5-year risk of conversion to MCI and AD using TAS Test results. There is a risk that not all participants classified as MCI will have prodromal AD (as MCI is a heterogeneous group with a variety of causes) but to account for this, we will perform post-hoc analyses of sub-groups with indicators of higher risk, for example, amnestic sub-type of MCI, p-tau181 positive, ApoE4, longitudinal cognitive decline. Data analysis and statistics will be performed in consultation with a biostatistician.

*Descriptive statistics*: The quantitative variables will be described using mean, standard deviation (SD) and range, or median and inter-quartile range if not normally distributed; Qualitative variables will be described using frequency and percentages.

*Test-retest reliability* will be assessed between the first and second completions of TAS Test at home (12 months), and between completions in the research centre and the home (3–6 months). Stability of the TAS Test assessments will be analysed by measuring the intra-class correlation coefficient and by use of Cohen’s kappa coefficient of agreement.

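### Aim 2's only cohort-wide validation uses a stable/declining label cut from PAL change with no stated allowance for test-retest error; adding a continuous PAL analysis would be a cheap gain

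*Protocol article*

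**What the plan says.** All references are to the protocol article.

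- Methods, Aim 2, Participants: each person receives one of two labels, stable or declining, and the label is set "depending on PAL total errors at baseline (30 or more) and an increase of more than 10 total errors at follow-up assessments". A published definition is cited for this rule.
- The same section admits "ISLAND participants who have completed ≥2 TAS Test and ≥ 2 CANTAB tests", so two CANTAB tests are enough for inclusion.
- Methods, Aim 2, Measurements: the data extracted include "CANTAB tests at baseline, + 24, and + 48 months", so PAL can be observed up to three times.
- Methods, Aim 2, Design: "We will invite 10,000 adults from a long-term cohort to complete online tests at home".
- Statistical analysis, Aim 2: the plan is to "predict cognitive trajectories (“stable” and “declining”) using ROC curve analysis". The other Aim 2 analysis is a "Bayesian multinomial logistic regression with regularizing priors to estimate the covariate adjusted log-odds of being in each diagnostic category at 5 years". It uses clinical diagnosis in the subsample of 300 and does not use the PAL label.

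The article gives no PAL standard deviation or reliability, no expected share labelled declining, and no precision target for the trajectory analysis.

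**The concern.** PAL total errors is a repeated numerical score. The plan reduces it to two classes by two fixed cuts, one on the baseline value and one on the raw change. A difference between two scores carries the error of both tests, so some unchanged people will cross the line by chance and some true decliners will miss it. Anyone who starts below 30 errors cannot be labelled declining if the rule is read literally. How far a person moves beyond the cut, or falls short of it, is not used.

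If labelling errors are unrelated to TAS Test, they pull the observed AUC towards 0.5, and a useful test can look weak. The diagnosis model cannot stand in for the ROC. It covers 300 people, who are chosen on their 48-month CANTAB scores. The ROC is therefore the only planned result that speaks for the whole cohort.

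**Working it through.** **The plan's own figure.** The only Aim 2 size calculation is for the 300-person diagnosis model. 0.33 ± 1.96 × √(0.33 × 0.67 / 300) gives 27.7% to 38.3%, which agrees with the stated 28-38%. It has no bearing on the PAL label, for which the article states no figure.

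**Inputs.** From the article: baseline cut of 30 or more, rise of more than 10, visits at 0, 24 and 48 months. Assumed, because the article gives none of them: 10% true decliners with a true rise of 15 errors by 48 months; PAL mean 15 or 25; between-person SD 10 or 15; SEM 3, 5 or 10 errors; normal errors; TAS Test with a true AUC of 0.80 against true decline and otherwise unrelated to the label.

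**Step 1, who is labelled.** With true mean μ, between-person SD s, SEM e and true change δ (0 or 15), observed baseline B has variance s² + e², change D has mean δ and variance 2e², and their covariance is −e². The share labelled is P(B ≥ 30 and D > 10) from the bivariate normal distribution.

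**Step 2, effect on AUC.** PPV is the share of those labelled declining who truly decline, and NPV the share of those labelled stable who truly do not. Each labelled group is a mixture of true decliners and others, so observed AUC = 0.5 + 0.3 × (PPV + NPV − 1).

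Example with SEM 5, mean 25, SD 15: 1.78% of unchanged people and 25.86% of true decliners are labelled.
- Labelled in all: 0.1 × 0.2586 + 0.9 × 0.0178 = 0.0419.
- PPV = 0.0259 / 0.0419 = 0.617.
- NPV = 0.9 × 0.9822 / 0.9581 = 0.923.
- AUC = 0.5 + 0.3 × 0.540 = 0.662.

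Ranges over the four mean and SD combinations, last-visit change:

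| SEM | Unchanged people labelled | True decliners labelled | PPV | Observed AUC |
|---|---|---|---|---|
| 3 | 0.02-0.2% | 6-32% | 94-97% | 0.76 |
| 5 | 0.2-1.8% | 5-26% | 62-77% | 0.66-0.70 |
| 10 | 0.7-4.8% | 5-19% | 30-43% | 0.57-0.60 |

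At SEM 3 nearly all of the small drop comes from true decliners who start below 30, not from test noise.

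**Step 3, the open reading of the follow-ups.** Simulated with a true rise of 7.5 at 24 months and 15 at 48 months:

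| SEM | AUC, either follow-up suffices | AUC, both required |
|---|---|---|
| 5 | 0.623-0.665 | 0.687-0.725 |
| 10 | 0.544-0.570 | 0.579-0.628 |

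**Step 4, information discarded.** For a normal variable cut so that a share p is labelled, with c the matching normal quantile, the information kept is φ(c)² / [p(1 − p)].
- p = 0.20: 0.2800² / 0.16 = 0.490, a loss of 51%.
- p = 0.10: 0.1755² / 0.09 = 0.342, a loss of 66%.
- p = 0.05: 0.1031² / 0.0475 = 0.224, a loss of 78%.

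These describe one cut on one normal variable, so they are a guide for the two-condition rule.

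**The case against.** Sensitivity and specificity need a binary reference, and the article says "we will assess the sensitivity and specificity of TAS Test to predict cognitive trajectories". A TAS Test x time term measures association, not discrimination. This stands: a two-class label is not an error for that purpose, and the ROC should stay.

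The label also follows a published definition that is not at hand, and whether one or all follow-ups count is a detail often left to an analysis plan. That is fair for the detail. Citing a definition does not remove measurement error in this cohort, and the cuts themselves are written into the article.

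Three stronger readings are tempting, and the documents do not support them.

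- A reader might infer that the label always rests on a single change. The rule also needs 30 or more errors at baseline, and the article speaks of follow-up assessments in the plural. One change is certain only for those with two CANTAB tests.
- A reader might apply the noise rate for a raw rise of more than 10, 1 − Φ(10 / (√2 × SEM)), which is 7.9% at SEM 5 and 24.0% at SEM 10. That ignores the baseline condition. With it, the rates in unchanged people are those in the working table, at most 4.8%.
- A reader might quote one fixed loss of information, such as a third to a half. The loss depends on the share labelled, which the article never gives.

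Lastly, everything turns on PAL reliability. With a small SEM the attenuation is slight, and that stands too. Power has not been shown to be limiting with 10,000 people invited.

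**Conclusion.** The point holds as a worthwhile, low-cost improvement, not as a flaw that invalidates Aim 2. The reference for the only cohort-wide validation is a hard cut on PAL scores with no stated allowance for test-retest error, while up to three PAL scores per person are available. Under the assumptions shown, a true AUC of 0.80 would be reported as anything from about 0.76 (SEM 3) to 0.57-0.60 (SEM 10) with last-visit change. The reading of the follow-up rule moves it further.

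The direction rests on labelling errors being unrelated to TAS Test. If TAS Test also tracks baseline PAL, the baseline condition could push the AUC the other way. The size rests on an SEM, PAL distribution and decliner share that the article does not give. The diagnosis model in the 300 is not affected.

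**What to change.** - Keep the stable/declining ROC for sensitivity and specificity, and state whether one or all follow-ups must show the rise.
- Report beside it, for the same cohort, a linear mixed model of PAL total errors over all available CANTAB visits, with baseline TAS Test x time as the tested term.
- Add a sensitivity ROC whose label comes from the model-estimated slope. Take that slope from a model without TAS Test, so that predictor and reference stay separate, and fix the cut in advance. Participants with two CANTAB tests can stay in, although their slopes will be less certain.
- State that the raw-change AUC is attenuated by measurement error, to the extent that the error is unrelated to TAS Test.

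No new data are needed. The cost is one more cohort analysis and one sensitivity ROC to specify and report, and the slope term answers a question of association rather than discrimination.

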### Sample size

#### Aim 1

We estimate that 17% (or 85 individuals) in the cognitively unimpaired THBP & HBA cohorts will have p-tau181 in the preclinical AD range [45]. We have performed ROC curve analysis using open data from Mollica et al. [19]. This showed area under ROC curve (AUC) of 0.75 for a null linear model including age, sex, ApoE4, and years of education, but not finger tapping, to detect p-tau181 positivity in CSF. To develop the multivariable model, power calculation showed the sample size to compare a screening test with an area under the curve (AUC) > 0.90 against the null model would require 60 positive p-tau181 cases and 290 controls. Thus, we will use 350 in the development dataset (expected 60 [17%] preclinical AD cases) and 150 in the validation dataset (expected 25 [17%] preclinical AD cases) to test cut-offs from the development model. The PROBAST tool [46] confirmed these combined development and validation strategies lower the risk of bias.

#### Aim 2

Based on the age distribution of ISLAND participants, we project that 8.6% of participants currently aged 70–74 years (a cohort of ~ 1300 from the 10,000 recruited) will develop dementia, and more than 16% of the 700 participants currently aged 75+ years will develop dementia over the study duration [47, 48]. Thus at least 200 participants will meet diagnostic criteria for dementia or MCI. Our sample size calculation aims to ensure precise estimation of model parameters while minimising potential of overfitting. A sample of 300 including 100 dementia cases would ensure accurate prediction of the outcome proportion (33%) with a targeted confidence interval of 28–38%. To target a mean absolute prediction error (MAPE) < 0.05, as recommended by Riley et al. [49], a sample of 300 would be adequate for up to 6 predictors in a parsimonious, statistically determined risk prediction model.

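### The 300-person clinic sample is drawn on 48-month CANTAB status, yet the model fitted in it is said to give absolute 5-year MCI and AD risk, with no correction for the sampling stated

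*Protocol article*

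**What the plan says.** Protocol article, Methods, Aim 2, Participants: a clinic sample of 300 is taken "from the larger cohort of up to 10,000 participants". For the first part, "we will invite 200 ISLAND participants (randomly selected) from those who have CANTAB scores (at the 48 month test point", the scores being those that suggest MCI or AD. For the second part, "A further 100 will be selected as age- and sex-matched controls from the Aim 2 participant cohort", from people whose CANTAB scores are unimpaired.

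Statistical analysis, Aim 2: a Bayesian multinomial logistic model with regularising priors is fitted in the sub-sample of 300. The categories are unimpaired, MCI and AD, and the candidate covariates include age and sex. The model is to "estimate posterior highest density intervals for 5-year risk of conversion to MCI and AD using TAS Test results". No sampling weight, offset or recalibration is mentioned. A separate ROC analysis of stable versus declining trajectories is not described as confined to the 300.

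Sample size, Aim 2: "A sample of 300 including 100 dementia cases would ensure accurate prediction of the outcome proportion (33%) with a targeted confidence interval of 28–38"%. It adds that "a sample of 300 would be adequate for up to 6 predictors in a parsimonious, statistically determined risk prediction model".

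**The concern.** Who enters the 300 depends on CANTAB at month 48, a close proxy for the clinic diagnosis the model predicts. The two-to-one ratio is set by the investigators, so the proportion with MCI or AD in the sample says little about that proportion in the cohort. A model fitted to the sample without adjustment takes its intercepts from the sampling ratio. Controls are also matched on age and sex, so the sample no longer shows how outcome frequency varies with those two variables, yet both are candidate covariates.

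Absolute 5-year risk is what Aim 2 is meant to deliver. If it is overstated, people at low risk are labelled as higher risk by a tool intended for screening. Checking calibration inside the same 300 would not reveal this, because the fitted and observed proportions would share the distortion.

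**Working it through.** **1. The plan's own figures**
- Interval: 0.33 ± 1.96 × √(0.33 × 0.67 / 300) gives 27.7% to 38.3%, against 28–38% stated.
- Predictors: the standard formula for mean absolute prediction error (MAPE) with a binary outcome is n = exp[(−0.508 + 0.259 ln φ + 0.504 ln P − ln MAPE) / 0.544]. With φ = 0.33, P = 6 and MAPE = 0.05, n = 300.4.

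Both figures reproduce, using 33% as the outcome proportion and all 300 people at equal weight.

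**2. The 33% against the plan's projections**
- Projected dementia: 0.086 × 1,300 + 0.16 × 700 = 111.8 + 112 = 224 cases.
- This is 11.2% of the 2,000 people aged 70 or over. It is 2.2% of 10,000 if nobody under 70 is affected, which is a floor.
- 33% is 3.9 times the projection for ages 70–74 and 2.1 times that for 75+.

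**3. Odds inflation from the draw**

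Inputs from Aim 2, Participants: CANTAB sensitivity/specificity of 97/81% for MCI and 82/97% for early dementia. Assumptions: 10,000 people, 224 with dementia, 500 to 1,500 with MCI, and an MCI cut that detects all dementia.

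*MCI cut, 500 MCI*
- Positives: 0.97 × 500 + 224 + 0.19 × 9,276 = 2,471. Negatives: 7,529.
- Sampling fractions: 200/2,471 = 0.0809 and 100/7,529 = 0.0133.
- An unimpaired person is drawn with probability 0.19 × 0.0809 + 0.81 × 0.0133 = 0.0261.
- Odds inflation, dementia versus unimpaired: 0.0809 / 0.0261 = 3.1.
- Expected dementia cases in the 300: 224 × 0.0809 = 18.

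*MCI cut, 1,500 MCI*
- Positives: 1,455 + 224 + 0.19 × 8,276 = 3,251. Negatives: 6,749.
- Sampling fractions: 0.0615 and 0.0148.
- Odds inflation: 0.0615 / (0.19 × 0.0615 + 0.81 × 0.0148) = 2.6.
- Expected dementia cases: 14.

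*Dementia cut*
- Positives: 0.82 × 224 + 0.03 × 9,776 = 477. Negatives: 9,523.
- Sampling fractions: 0.419 and 0.0105.
- Odds inflation: (0.82 × 0.419 + 0.18 × 0.0105) / (0.03 × 0.419 + 0.97 × 0.0105) = 0.346 / 0.0228 = 15.2.
- Expected dementia cases: 224 × 0.346 = 77.

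No scenario yields the 100 dementia cases that the sample-size text assumes.

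**4. Direction**

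With a two-to-one draw inside an age-sex stratum, risk is overstated wherever fewer than two-thirds of the stratum are CANTAB-positive. At 97/81%, solving 0.97p + 0.19(1 − p) = 2/3 gives p = 0.61. The direction therefore holds until about 61% of a stratum truly has the outcome.

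**5. Simulation**

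Assumptions: a binary outcome; risks of 1% under 70 (assumed), 8.6% at 70–74 and 16% at 75+; one standardised predictor with log-odds 1.00; CANTAB errors unrelated to that predictor given the outcome; controls matched on age only. The draw was scaled up in proportion to remove noise.

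| CANTAB accuracy | Age band | True mean risk | Unweighted | Weighted |
|---|---|---|---|---|
| 97/81% | under 70 | 1.0% | 3.2% | 1.0% |
| 97/81% | 70–74 | 8.6% | 20% | 9.0% |
| 97/81% | 75+ | 16.1% | 31% | 15.9% |
| 82/97% | under 70 | 1.0% | 13% | 1.0% |
| 82/97% | 70–74 | 8.6% | 41% | 8.4% |
| 82/97% | 75+ | 16.1% | 50% | 15.8% |

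The log-odds for 75+ against under 70 was truly 3.12. Unweighted it was 2.88 (97/81%) and 2.20 (82/97%); weighted it was 3.09 in both. The predictor's own coefficient was hardly affected unweighted (1.01 and 0.99).

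**6. Cost of weighting**

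The effective sample (Kish) is (Σw)² / Σw². With 500 MCI, the weights are 12.4 for 200 people and 75.3 for 100, giving 10,000² / (200 × 12.4² + 100 × 75.3²) ≈ 167. With 1,500 MCI it is about 197. At the dementia cut it is about 110.

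**The case against.** The strongest reply is that the article is silent on weights and does not rule them out. It condenses a fuller plan, uses stratified random sampling for the controls, and promises biostatistical input. A reader might infer that the protocol commits to an unweighted fit, and the text does not support that. What can be said is that no correction is stated. The point still stands, because the article itself fixes the outcome-dependent sample, the model fitted in it, the absolute-risk claim, and a sample-size argument that takes 33% as the outcome proportion.

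A second reply is that logistic regression tolerates case-control sampling. That protects odds ratios when selection depends only on the modelled outcome; it does not protect absolute risk. Here selection is on an imperfect proxy and controls are matched on two candidate covariates. The simulation supports the reply for the test's own coefficient, but not for the risks or the age terms. Regularising priors shrink coefficients and do not restore the cohort frequency.

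A reader might also compare 33% with 2.2% and infer a 21.8-fold inflation of the odds (0.5 / 0.0229), so that a true 2% reads as about 31%. That holds only if 100 of the 300 have dementia and nobody under 70 does. The second condition is a floor, and the draw itself would give about 14 to 18 dementia cases at the MCI cut or about 77 at the dementia cut. On the 70-and-over base of 11.2% the corresponding factor is 4.0.

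Nor is every Aim 2 result affected: the probability of being unimpaired moves the other way, and the trajectory ROC analysis is not described as restricted to the 300.

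**Conclusion.** The concern holds for the MCI and AD risks from the 300-person model. Followed as written, they are overstated, the probability of being unimpaired is understated, and matching distorts the age and sex coefficients.

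The size cannot be fixed from the document, which gives no separate MCI frequency. Under the stated assumptions the odds of dementia versus unimpaired are inflated about 2.6- to 3.1-fold at the MCI cut, the closer reading since selection is on scores suggesting MCI or AD, and about 15-fold at the dementia cut. In that two-category comparison, a true 10% would read as about 22 to 26% at the MCI cut, or about 63% at the dementia cut. The direction is much firmer than the size.

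The sample-size arithmetic is correct as arithmetic. Its fault is to treat a proportion created by the selection as the proportion to be predicted.

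**What to change.** Keep the two-phase design; it is an efficient way to use 300 clinic places. Then:
- Record, for each CANTAB-by-age-by-sex stratum, how many were eligible, invited and attended. Attendance matters because the 200 are invited, and the Discussion accepts that some people may not want to know their dementia risk.
- Fit the multinomial model with inverse-probability weights from those fractions (weighted or pseudo-likelihood). A simple intercept shift is only approximate, because selection is on CANTAB and not on the diagnosis.
- Check calibration against the weighted outcome rate in the Aim 2 cohort.
- Do not report unweighted absolute risks. If weighting is not adopted, limit the claim to relative associations.
- In Sample size, Aim 2, say that 33% is a sampling proportion and not the cohort risk, and restate the precision and the number of predictors for the weighted analysis.

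No extra clinic visits are needed, but the change goes beyond wording. Intervals widen, with an effective sample of about 167 to 197 at the MCI cut or about 110 at the dementia cut, before any further loss from uneven age-sex strata or attendance. The present case for six predictors would have to be remade on that basis.
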